#### Re-design of the garden

The landscape architects in the project will make a program with specific design criteria and design solutions based on landscape analyses, the outcomes of the exploration of best-practice cases, the literature searches, and the co-design process. This program will form the base of the actual re-design of the garden. Staff and the co-design group will be able to provide feedback on the final design during workshop 4, however, it is important to note, that all their wishes for the garden will not necessarily be fulfilled. The actual garden renovation will be carried out by external partners (for example, landscape gardeners) during winter season, based on the design provided by the landscape architects.

#### Implementation phase

During this phase, the new garden design is implemented. To ensure the staff's interest in garden activities in a broader sense and their willingness to accept responsibilities, a garden team is formed among them. The care staff is extremely important to involve and inform throughout the project period, as it is this group that, after completing the project, must ensure the continued use of the garden through meaningful activities.

Integrating garden activities into the nursing home's culture is one of the objectives of the implementation phase. Staff of three out of the six units at the nursing home will be required to facilitate garden activities for all residents at the three units two times a week for one month. Care staff will be asked to talk about practical experiences in the garden as they accumulate greater expertise throughout the implementation period. As a result, they become better at facilitating garden activities, and the new knowledge may become a part of their professional identities. The co-design group will simultaneously evaluate the tested garden activities, and a yearly cycle of events is planned for the PwD, their relatives, and staff members during all the seasons and special occasions. The project will require the creation of brief activity descriptions (idea cards), and examples of how staff and PwD might contribute to various activities must be described. The purchase of supplementary equipment (pruning shears, warm blankets, firewood, plant tables, pots, flower seeds, etc.) will enable the staff to begin garden activities with the PwD. The co-design team and staff will attend a follow-up workshop to discuss how gardening activities can be practically incorporated into daily care and fulfill the needs of PwD, especially those related to BPSD.

### Post-intervention

In the post-intervention, it is crucial to make sure that the nursing home staff anchors and develops relevant garden activities. Short lectures or workshops on using the garden and developing new activities are offered during monthly staff meetings, when the staff's experiences are included, and new ideas are produced. To ensure that activities in the garden are maintained all year long, this process will be initiated by the nursing home's garden team, who will also have the chance to communicate with the research team for a full year after the project is finished. To further the project's initiatives for generating experiences and long-term anchoring of activities in and usage of the garden, the garden group also passes significant experiences to the research group.

### Evaluation measurements

As described previously, the study consists of an effect evaluation across four data collection time points, and a continuous process evaluation across all four study phases. Each evaluation has their own data collection methods and measures, described in more detail below.

#### Effect evaluation

The aim of the effect evaluation is to examine the use of – and the effect of using the renovated and implemented garden for residents and care staff. The pre- and post-intervention effect evaluation will consist of: 1) systematic objective observations of garden users; and 2) questionnaire administered to staff on staff burnout and garden use. The pre- and post-implementation effect evaluation will consist of: 1) the The Neuropsychiatric Inventory Nursing Home version (NPI-NH) clinical instrument on residents’ BPSD symptoms and staff’s work disturbances; and 2) medication use.

##### Pre- and post-intervention

Systematic observations are conducted using a camera solution called HallMonitor developed by Webitall Aps [44]. The HallMonitor-system uses a cloud-based software platform and a number of cameras mounted on the wall. Each camera unit is configured to take a picture every half hour within a specified time-period, for example, from 6 am to 11 pm. HallMonitor uses a GDPR compliant design in which the camera takes a picture and immediately sends it through an encrypted 3G or 4G connection to a cloud-based platform storage which only Webitall has access to. The original picture is deleted from the camera unit after it has been sent to the platform. An automated script on the software platform processes the pictures automatically through a neutral network, which counts all the people in each picture whereafter the picture is being blurred. This process takes less than 10 min to complete. The unit has its own cellular data connection and only requires power to operate, making it easy to use in different settings. The camera system is so far mainly used by municipalities and sports associations to collect data on how different sports facilities are used by the public. This will be the first time that the system is used within nursing homes. Camera observations will be done for one month during August 2022 (pre-intervention), and at the same time one year later (August 2023) during post-intervention to systematically assess whether the intervention will increase the use of the garden. Cameras are placed to collect data from 6 am in the morning until midnight for 30 days, taking a momentary picture every 15 min. Four cameras are placed inside the nursing home, facing out into the garden, and one camera is placed inside the green house, to ensure that the whole garden is captured on camera. Additionally, one camera is placed on each balcony facing the garden, to detect any use of the balcony to get into the garden, giving a total of six cameras. The compiled data makes it possible to determine the number of users at different times and days of the week and month, as well as assess which parts of the garden are being used.

The questionnaire administered to staff related to staff burnout is based on Pines’ scale measuring a person’s feelings at work [45]. The scale consists of 21 items with responses stated on a seven-point scale going from ‘never’ (1) to ‘always’ (5). A person is regarded at risk of developing physical-, emotional- and/or mental exhaustion if they score between 3.0 and 4.0, whereas > 4.0 is considered experiencing and exhibiting symptoms of burnout [46]. Pines has tested the instrument for reliability and validity [45] and Åström et al. showed in their study high internal consistency and consistency between burnout scores and separate performed interview questions on burnout [47]. The instrument has previously been used in several studies [46–50], however, the instrument has, to our knowledge, not been previously used in a Danish context, and was therefore translated into Danish by the research team. The translation was performed by two researchers, who afterwards compared the translations and agreed on a common translation in case of inconsistencies. Additional questions were included in the questionnaire regarding staff’s garden use and attitude towards garden use (see Additional file 2). The questionnaire will be administered to staff through an e-mail send by the nursing home manager during July 2022 and again in July 2023. The staff will be given two weeks to complete the questionnaire and will be receiving a reminder e-mail after one week.

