### Aim

This paper will present the study protocol of the ‘Gardens for People with Dementia’ study. The aim of the study is to develop and implement a nature-based palliative rehabilitation intervention on how nursing home gardens can be used by PwD to improve a range of health outcomes. The paper includes a description of the study case, the co-design-based re-design of a nursing home garden and development of a nature-based palliative rehabilitation program, the implementation of the nursing home garden, and measurements used in the process- and effect evaluation of the study.

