#### The garden

The nursing home is located within a social housing estate that was established between 1970 and 1980 and refurbished between 2006 and 2020 by C.F. Møller Architects, a well-acknowledged Danish architecture firm. C.F. Møller also designed the nursing home's garden and the adjacent green spaces, including a playground/activity area.

The garden is oriented to the west, which provides sun from midday till sunset; however, this also means that the garden and the balconies facing the garden are exposed to wind most of the time, as this is the most prevalent wind direction in Denmark. The garden is in generally good condition and is very well maintained by volunteers from a local socioeconomic initiative (see Fig. 2).

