### Data analysis

#### Effect evaluation analysis

##### Pre- and post-intervention

The systematic camera observations will provide information on how many people are using the garden and which parts of the garden they are using before and after the intervention, 24/7 and for a whole month. This will provide information on whether more people are using the garden after the intervention and if they are using the renovated parts of the garden. As the camera is taking four pictures per hour, the amount of data at the end of each data collection will be 20,160 blurred pictures. For each picture, the cloud-based software platform will provide the number of people in the picture, which will be a data point in the dataset. Consequently, the dataset will consist of 20,160 datapoints sorted by date at baseline and the same amount again at follow up. The blurred pictures are used to identify which areas of the garden are being used. The garden will be divided into several zones and each zone will be given a number. A student assistant will go through all pictures and classify in which zones people are observed and how many people are observed in the zones. The differences between pre- and post-intervention observation data will be analyzed as repeated cross-sectional measures as person identification is not possible.

The collected survey data on staff burnout and use of the garden completed by staff, will be uploaded into the statistical software IBM SPSS Statistics version 28. The differences between pre- and post-intervention will be analyzed as repeated measures comparing the degree of job satisfaction, use of garden, and attitude towards use of garden. This will provide information on whether the intervention has decreased staff burnout and has changed their use of the garden and their attitude towards using the garden in the daily care of PwD.

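### The camera outcome is a head count with no coding of who is present, so a rise between the two Augusts shows more persons in the garden, not more use by people with dementia

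*Protocol article*

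**What the plan says.** All references are to the protocol article.

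- **Automated step** (Effect evaluation, Pre- and post-intervention). Pictures are processed by software "which counts all the people in each picture whereafter the picture is being blurred". The purpose is "to systematically assess whether the intervention will increase the use of the garden", comparing August 2022 with August 2023.
- **Data point** (Data analysis, Pre- and post-intervention). For each picture, "the cloud-based software platform will provide the number of people in the picture, which will be a data point in the dataset".
- **Manual step** (same section). The student assistant goes through all blurred pictures to "classify in which zones people are observed and how many people are observed in the zones".
- **Analysis and stated inference** (same section). The differences "will be analyzed as repeated cross-sectional measures as person identification is not possible". On interpretation: "This will provide information on whether more people are using the garden after the intervention".
- **Aim** (Aim). The intervention concerns "how nursing home gardens can be used by PwD to improve a range of health outcomes". The Background names underuse by those living with dementia in particular, and Learning from a single case sets the goal of making garden use part of residents' daily care.
- **Other people in the garden.** The section The garden describes it as "very well maintained by volunteers from a local socioeconomic initiative". The nursing home has 75 care staff. The co-design section invites staff to garden experiences for their own well-being, and the Implementation phase section forms a staff garden team, which the Post-intervention section has keep activities going.

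**The concern.** The outcome and the aim refer to different groups of people. The outcome counts everyone in view, while the aim concerns residents with dementia. The difference would matter less if non-resident presence were a stable background, but the project is designed to change it. Staff are encouraged to use the garden, a garden team is set up, and both happen between the two camera periods.

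No other effect measure fills the gap. The staff questionnaire is described as covering staff's own garden use and attitude, residents are not interviewed, and no log of resident outings is described.

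At stake is the reading of a positive camera result. If it is reported as increased use by people with dementia, the data will not support the statement. No later analysis can recover a role that was never recorded.

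**Working it through.** **1. The plan's own figure.** The only figure given for the camera data is 20,160 pictures per collection. The stated schedule (06:00 to midnight, four pictures an hour, 30 days, six cameras) gives 18 × 4 × 30 × 6 = 12,960. The stated figure would follow from 24 × 4 × 30 × 7 = 20,160, or from 18 × 4 × 28 × 10 = 20,160; neither matches the described set-up. This is a separate inconsistency, and the present point does not depend on it.

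**2. What is recorded at each step.**

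| Step | Recorded | Role recorded? |
|---|---|---|
| Software | Number of people in the picture | No |
| Student assistant | Zone, number of people per zone | No |
| Staff questionnaire | Staff's own use and attitude | Staff only; not a count of residents |

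Counts can also be split by time, day and area. None of these splits separates residents from others.

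**3. Identification.** Let *s* be the residents' share of the baseline count, *r* the relative change in resident presence and *g* the relative change in non-resident presence. The relative change in the total is

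total change = *s* × *r* + (1 − *s*) × *g*.

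Only the left-hand side is observed. The documents give none of *s*, *r* or *g*, so every value below is an assumption.

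*Residents unchanged* (*r* = 0), so the total change is (1 − *s*) × *g*:

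| Resident share *s* | *g* = +25% | *g* = +50% | *g* = +100% |
|---|---|---|---|
| 30% | +17.5% | +35% | +70% |
| 50% | +12.5% | +25% | +50% |
| 70% | +7.5% | +15% | +30% |

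*Total observed to rise 25%*, solved for residents: *r* = [1.25 − (1 − *s*)(1 + *g*)] / *s* − 1.

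| Resident share *s* | *g* = −25% | *g* = 0 | *g* = +25% | *g* = +50% |
|---|---|---|---|---|
| 30% | +141.7% | +83.3% | +25% | −33.3% |
| 50% | +75% | +50% | +25% | 0% |
| 70% | +46.4% | +35.7% | +25% | +14.3% |

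For example, with *s* = 0.3 and *g* = 0.5: (1.25 − 0.7 × 1.5) / 0.3 − 1 = 0.20 / 0.3 − 1 = −0.333. The same 25% rise in the total is therefore compatible with residents using the garden more, equally or less.

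**The case against.** The strongest reply is that the protocol never says the cameras measure resident use. It speaks of use of the garden and of more people, and the Effect evaluation section covers residents and care staff, so staff presence is partly intended. Severely demented residents rely on staff to go outdoors, so staff counts partly follow resident outings. The study is exploratory, names no primary outcome, and reads the cameras beside a questionnaire and interviews. All of this stands, and it makes the fault a mismatch between outcome and aim. It does not remove it: if both groups are of interest, a total that cannot separate them answers for neither.

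A reader might infer several stronger things that the documents do not support.

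- *That role cannot be seen in the pictures.* The text says that persons cannot be identified and plans no role coding. Whether a wheelchair or maintenance work is visible after blurring is not stated.
- *That contractors inflate the 2023 count.* External landscape gardeners appear only for the winter renovation, outside both Augusts. The maintenance volunteers remain, and they already tended the garden at baseline; whether the redesign brings more maintenance is not stated.
- *That the required activity month falls in the camera window.* The twice-weekly month lies between the March and May 2023 assessments. Staff use that persists into August would be an intended effect, though still not evidence on residents by itself.
- *That organised events should be removed as contamination.* Facilitated activities with residents are the intervention. Dropping them would bias the comparison towards no effect.

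**Conclusion.** The point holds as a limit on interpretation. On the current text the camera outcome is a total head count with no role coding at either step. A rise between the two Augusts shows that more persons were present; it does not show that people with dementia used the garden more.

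The size of the possible error cannot be derived from the documents. Under the assumed mixes, non-resident growth of 50% alone raises the total by 15% to 35%, and a 25% rise in the total leaves even the sign of the resident change open. These figures illustrate the problem and do not forecast the result.

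A reader might go further and infer that the protocol claims a resident effect, or that the study's success hangs on the cameras. It does neither. The data remain usable for what they count, and the change is worth making because the extra information can be collected in a review that is already planned.

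**What to change.** 1. In the student assistant's review of all blurred pictures, add one field for apparent role where the picture allows: for example wheelchair or walking aid, accompanied group, maintenance work, undetermined. Code both Augusts by the same written rules. Report the share undetermined, and state that residents who walk independently may be missed. The field does not require identifying anyone.
2. Keep a calendar of maintenance and research visits in both Augusts and give the comparison with and without those slots. If August 2022 has passed, rebuild its calendar from the home's records.
3. Keep organised resident activities in the main count, and also show them separately.
4. Name the outcome *persons present in the garden*, and do not conclude increased resident use from the total alone.

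The cost is a little more coding, a simple calendar and a more modest conclusion. The role field will be imperfect, so it should qualify the total and not replace it.

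### Garden use is compared between August 2022 and August 2023 in one garden, with no concurrent control and no weather data described, so year-to-year weather could create or hide an apparent change

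*Protocol article*

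**What the plan says.** Under Evaluation measurements, Effect evaluation, Pre- and post-intervention, cameras record the garden for a month in August 2022 and for the same month in 2023. The schedule is: "Cameras are placed to collect data from 6 am in the morning until midnight for 30 days, taking a momentary picture every 15 min". The stated purpose is "to systematically assess whether the intervention will increase the use of the garden". On what the cameras yield, the section says: "The compiled data makes it possible to determine the number of users at different times and days of the week and month". It adds that the data show which parts of the garden are used. No weather variable is listed.

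Under Data analysis, Effect evaluation analysis, Pre- and post-intervention, the method is one sentence: "The differences between pre- and post-intervention observation data will be analyzed as repeated cross-sectional measures as person identification is not possible". On interpretation, the section says: "This will provide information on whether more people are using the garden after the intervention". The counts are described as sorted by date.

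The section The garden describes a west-facing site and notes that "the garden and the balconies facing the garden are exposed to wind most of the time".

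The only concurrent contrast is in Implementation phase: "Staff of three out of the six units at the nursing home will be required to facilitate garden activities" for one month. That contrast is evaluated by NPI-NH and medication use in March and May 2023. It is not evaluated by the cameras, which cover the shared garden.

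**The concern.** The comparison asks a causal question of one month before and one month after, in one garden. Whether people go outdoors depends on the weather, and the article itself describes an exposed site. Repeating the measurement in August removes season as an explanation. It does not make the two Augusts alike in rain, temperature or wind.

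The section Pre- and post-implementation accepts the one-year gap because the data are collected as repeated cross-sections. That design avoids having to follow individuals whose dementia progresses. It gives no protection against conditions that differ between the two occasions.

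At stake is the study's objective measure of garden use. A kinder August 2023 could look like an intervention effect, and a poorer one could hide a real gain.

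**Working it through.** **The plan's own figure.** The only number given for this outcome is 20,160 pictures per collection period. The stated schedule gives 4 per hour × 18 hours × 30 days × 6 cameras = 12,960. The figure 20,160 equals 4 × 24 × 30 × 7. This mismatch needs reconciling, but it is a separate matter and does not affect the present point. The article gives no expected count, effect size or weather response, so everything below rests on assumed inputs.

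**Apparent ratio with no intervention effect.** Let f₀ and f₁ be the dry (fair) days out of 30 in the two months, and k the ratio of use on a fair day to use on a poor day. If the intervention does nothing, the expected ratio of monthly counts is

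(f₁·k + 30 − f₁) / (f₀·k + 30 − f₀).

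With 20 dry days in one August and 14 in the other:

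| k (assumed) | Calculation | Ratio |
|---|---|---|
| 1.5 | (30 + 10)/(21 + 16) = 40/37 | 1.08 |
| 2 | (40 + 10)/(28 + 16) = 50/44 | 1.14 |
| 3 | (60 + 10)/(42 + 16) = 70/58 | 1.21 |
| 5 | (100 + 10)/(70 + 16) = 110/86 | 1.28 |

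If the wetter month comes second, the ratios invert: 37/40 = 0.93 at k = 1.5 and 86/110 = 0.78 at k = 5.

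**Other assumed day counts, same formula.** A rise from 15 to 20 fair days gives 1.07 (k = 1.5) to 1.22 (k = 5). A rise from 12 to 20 gives 1.11 to 1.41. A fall from 20 to 15 gives 0.94 to 0.82.

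**Error rate of a crude test.** A simulation with no true effect (20,000 runs, 40 head counts per day, mean fair-day share 0.55) compared the two monthly totals by a Poisson test at a nominal two-sided 5%.

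- With chance day-to-day weather only, the test was significant in 22% of runs at k = 1.5 and in 63% at k = 5.
- With a between-year SD of 0.10 in the fair-day share, the figures were 35% and 75%.
- With the weather effect removed, the rate returned to about 5%.

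Two limits apply. The article does not specify this test. The adjusted run also used the true weather effect, so it shows the best that adjustment can do.

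**The case against.** The strongest reply is that this is a missing covariate in a condensed article, and that adjusters are commonly left to an analysis plan. Nothing has to be collected prospectively, since weather records can be linked later. The study also calls itself single-case and exploratory, and staff garden use is surveyed in July of both years.

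Part of this stands. An unseen plan may contain weather terms, so the point can be made only of what the article describes. But the uncontrolled two-month comparison and its causal purpose are fixed in the article. The exploratory label and the disclaimer on generalizability concern external validity, whereas this is a question of internal validity. The staff survey is another before-after measure, so it supports the cameras without supplying a control.

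The objections to size also stand. The 28% needs a fivefold ratio, and milder ratios give much less. A day-level analysis would absorb chance daily weather into its residual variance, leaving the between-year shift, so the simulated error rates should not be read as those of the study. The wind remark describes a standing feature present in both years: it shows that weather matters at this site, not that it differed.

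A reader might also infer three things that the document does not support:

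- **That weather could swamp the effect of interest.** No effect size is stated, so this cannot be judged.
- **That project events distort the counts.** The software counts everyone in each picture, but no project-run event is dated to a camera month.
- **That volunteers distort the comparison.** Volunteer upkeep is described as ongoing, and nothing shows that it changes between waves.

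**Conclusion.** The concern holds in limited form. As described, the garden-use result is a crude before-after difference from one garden. Season is matched, but year-to-year weather is neither measured nor controlled. The bias can run either way.

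Its size is not derivable from the document. About 8% to 28% is an illustration for 20 versus 14 dry days of 30 and assumed use ratios of 1.5 to 5, not an estimate for this site. Nor does the document show that a favourable August would in fact be credited to the intervention. The purpose statement is causal, but the analysis section speaks only of use after the intervention. The measure remains usable; its causal reading needs the step below.

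**What to change.** - Take daily rain, temperature and wind for both camera months from a public weather station and link them to the date-sorted counts.
- Fit a day-level pre/post model with weather and weekday/weekend terms. Weather varies from day to day within each month, so its effect can be separated from the pre/post term.
- Report the adjusted figure, and use on comparable-weather days, beside the crude figure.
- Word the result as an adjusted before-after difference, because weather terms will not remove other differences between the two years.
- At most, note any research-team-run event that falls in a camera month and examine it in a sensitivity analysis.

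Two further steps might suggest themselves, and I would leave both out. The number of residents varies little within a month, so it would be nearly collinear with the pre/post term. Excluding days with garden activities could delete the very effect sought, since maintained activity is the aim of the post-intervention phase.

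The cost is small: public data and a few model terms, with no change to data collection. The downside is some loss of precision with about 60 days (2 × 30).
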